### Data analysis

Data analysis will be carried out using NVivo software for qualitative data and Stata (Version 16) for quantitative data. For the FGD data, emerging themes will be assessed using the NVivo software. Count and binary data will be analysed using Generalised Linear Models. Data analysis will be carried out using cluster level summaries since random effects models perform poorly in a matched design with fewer than 20 clusters per arm [28]. For the primary endpoint of mosquito density, the ratio of densities in each matched pair will be calculated and inference will be based on a paired *t*-test. Adjustment will be made for time post-spraying, LLIN use and wall type using the two-stage method described by Hayes and Moulton [28]. The secondary outcomes of EIR, sporozoite rate, estimated number of infective bites per person per year, and residual bioefficacy will be analysed in the same way.

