## Study objectives

### Primary objective

To determine non-inferiority of VECTRON™ T500 to the reference product Fludora® Fusion (Bayer AG, Monheim, Germany), which has been prequalified by WHO PQT/VCP, in reducing vector population density. This will be determined by the difference between the number of female *An. gambiae* sensu lato, *An. funestus s.l.* and *Culex* spp*.* caught per trap night in clusters sprayed with VECTRON™ T500 compared to Fludora® Fusion. Individuals from morphologically identical species complexes will be identified to species level using molecular diagnostics.

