### Power calculation, estimation of effect size and cluster selection

Sample size calculations will be based on the study primary endpoint i.e., indoor density of *Anopheles* mosquitoes. An estimated mean of 3.0 female *Anopheles* per light trap per night will be used, referencing data from recent studies in Tanzania [27]. A paired design will be used in which clusters will be matched on baseline indoor density of *Anopheles* mosquitoes. Previous data suggests a within-pair coefficient of variation of 0.23, but a conservative value of 0.3 will be used in our calculations.

The trial is a non-inferiority design, intended to show that spraying the intervention product, VECTRON™ T500, will not result in higher malaria vector densities, by a prespecified non-inferiority margin of 50%, than those per trap per night in the reference arm sprayed with Fludora® Fusion. Using the methods described in Hayes and Moulton [28] and the assumptions listed above, it was calculated that 8 clusters per treatment arm (16 in total) will be needed for the 50% margin to have 80% power to demonstrate non-inferiority. The calculations were based on 49 trap nights per cluster. There was very limited statistical advantage in increasing trap-nights beyond 50. This number of clusters considers the loss of degrees of freedom caused by matching.

Sixteen clusters, containing 75–200 households per cluster (HHs), will be selected for spraying. Core areas of clusters should be at least 1 km apart to prevent infiltration of mosquitoes from other villages. All consenting HHs in all 16 clusters will be sprayed. Approximately 1200–3200 households will be sprayed (~ 75–200 HHs/cluster in 16 clusters).

Although a minimum of 49 households is required per cluster according to the sample size calculations, a larger hamlet will be recruited for logistical reasons, as a proportion of households may refuse to accept the IRS spraying and others may be absent during spraying or lost during follow-up.

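### The primary objective is worded as a difference while the margin and analysis are relative, and the scale of the t-test on the pair ratios is not stated

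*Protocol article*

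**What the plan says.** Three places in the protocol article bear on the primary comparison.

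- *Primary objective*: "This will be determined by the difference between the number of female" mosquitoes caught per trap-night in the two arms.
- *Power calculation, estimation of effect size and cluster selection*: the new product "will not result in higher malaria vector densities, by a prespecified non-inferiority margin of 50"%, relative to the reference arm. The planning inputs stand in the same section: "An estimated mean of 3.0 female" *Anopheles* per trap-night, and "Previous data suggests a within-pair coefficient of variation of 0.23, but a conservative value of 0.3 will be used in our calculations". On these, "it was calculated that 8 clusters per treatment arm (16 in total) will be needed" for 80% power, with 49 trap-nights per cluster and an allowance for the degrees of freedom lost by matching.
- *Data analysis*: "the ratio of densities in each matched pair will be calculated and inference will be based on a paired" *t*-test. It adds: "Adjustment will be made for time post-spraying, LLIN use and wall type using the two-stage method described by Hayes and Moulton".

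The article does not say whether the ratios are logged. It does not restate the margin as a limit for the ratio, and it names neither alpha nor a confidence level.

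**The concern.** The objective is on a difference scale, while the margin and the analysis are on a ratio scale. Read literally, the analysis sentence has two steps, form the ratio and then apply a *t*-test, with no log between them.

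That matters because the arithmetic mean of raw ratios is not centred on 1 when the products are identical, and it is not symmetric. VECTRON/Fludora and Fludora/VECTRON both average above 1, so the result depends on which arm is put on top, and the article does not say which. The choice of scale also affects power, and it may not be the scale on which the number of clusters was worked out.

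**Working it through.** **Inputs.** From the article: mean L = 3.0 per trap-night; within-pair coefficient of variation k = 0.30 (0.23 from previous data); y = 49 trap-nights per cluster in the calculation and 180 over 12 months in the Vector density section; 8 pairs; margin 50%; power 80%. Assumed: one-sided alpha 2.5%, with 5% as the alternative; 2 clusters per arm added for matching; equal true densities; Poisson catches within clusters.

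**1. The plan's own figure.** Take the margin as an absolute d = 0.5 × 3.0 = 1.5:

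`c = 2 + (z_alpha + z_beta)² × [2L/y + k² × 2L²] / d²`

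`= 2 + 7.849 × [6/49 + 0.09 × 18] / 2.25 = 2 + 7.849 × 1.742 / 2.25 = 8.08`

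Power at 8 pairs is 79.5% by this formula and 79% by the noncentral *t*. This matches the stated 8 clusters and 80%. At one-sided 5% the formula gives 6.79.

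**2. The same inputs on the log-ratio scale**, margin ln 1.5 = 0.4055:

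`c = 2 + 7.849 × 2 × (0.09 + 1/147) / 0.4055² = 2 + 7.849 × 0.1936 / 0.1644 = 11.24`

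At one-sided 5% it gives 9.28. With 8 pairs the standard error is √(0.1936/8) = 0.1556 and the noncentrality is 0.4055/0.1556 = 2.61. On 7 df, power is 61% (one-sided 2.5%) or 76% (5%).

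A figure of 8 can also be reached on the log scale by rounding up 7.70 (k = 0.23, one-sided 2.5%) or 7.28 (k = 0.30, one-sided 5%, nothing added for matching). Each of these departs from an input that the article states.

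**3. Bias of raw ratios.** For independent lognormal cluster densities with equal means, the expected ratio is 1 + k²: 1.09 at k = 0.30 and 1.053 at k = 0.23, before counting error. Simulation with Poisson counts and 49 trap-nights gives 1.10 to 1.11 and 1.06. The geometric mean ratio is 1.00 throughout.

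**4. Power with identical products** (200,000 simulated trials per setting, 8 pairs, upper limit compared with 1.5). Ranges cover gamma and lognormal cluster densities.

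| k | Trap-nights | One-sided alpha | Raw ratio | Log ratio |
|---|---|---|---|---|
| 0.30 | 49 | 2.5% | 53–56% | 59–62% |
| 0.30 | 49 | 5% | 64–67% | 74–77% |
| 0.30 | 180 | 2.5% | 56–60% | 62–65% |
| 0.30 | 180 | 5% | 66–70% | 76–79% |
| 0.23 | 49 | 2.5% | 75–77% | 80–81% |
| 0.23 | 49 | 5% | 84–86% | 90–91% |

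**5. Type I error** at a true ratio of 1.5 with k = 0.30: raw VECTRON/Fludora ratios reject in 2.1–2.2% of trials against 2.5% nominal, and 3.6% against 5%. The log analysis is close to nominal (about 2.5% and 4.9–5.0%).

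**The case against.** Much of the case on the other side stands.

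- **The word *untransformed* is not in the article.** A paired *t*-test on log densities is exactly a test of the log ratio, so the sentence is open to that reading. An article may also leave the transformation to the full protocol or analysis plan. What can be said is that the scale is not stated, not that the wrong one was chosen.
- **A reader might infer three incompatible scales.** There are two. The margin, "by a prespecified non-inferiority margin of 50%, than those per trap per night in the reference arm", is a ratio limit of 1.5 and fits the pair-ratio analysis. Only the objective's wording is out of line, and it may be loose phrasing: the secondary objective on *Culex* compares catches in the same way.
- **A reader might infer a fixed decision margin of 1.5 mosquitoes**, which would become too lenient if the reference mean fell below 3.0. The article sets no such rule. It ties the 50% to the density in the reference arm, and 3.0 is a planning value. The 1.5 used above only reconstructs the sample size.
- **A reader might infer that raw ratios inflate false claims of non-inferiority.** With VECTRON as numerator they do the opposite and are slightly conservative. The inverse orientation was not simulated.

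What remains is a mismatch inside the article between the objective and the analysis, an open scale on which the primary result depends, and a power figure that does not come back on the log-ratio scale from the stated inputs at either alpha considered.

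**Conclusion.** The concern holds in a limited form. The objective should match the ratio on which the margin and the analysis already agree, and the scale of the *t*-test should be fixed. Followed literally with raw VECTRON/Fludora ratios, the analysis would cost about 6 points of power at one-sided 2.5% or 10 points at 5% (k = 0.30), and about 4 to 6 points at k = 0.23. It would cost power, not validity.

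The larger numerical consequence is for the stated 80%. With k = 0.30, 8 pairs and 49 trap-nights, even the log-ratio test has about 59–62% power at one-sided 2.5%, or 74–77% at 5%. With 180 trap-nights at one-sided 5% it comes close to 80% (76–79%), and at k = 0.23 it reaches about 80% at one-sided 2.5%. That the planners worked on an absolute scale is an inference from the match at 8.08. It depends on the assumed alpha and on the 2 clusters added for matching.

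This should be corrected before the data are compared by arm, but it ranks below an error that would by itself invalidate the primary conclusion.

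**What to change.** 1. In the primary objective, replace *difference* with the ratio of densities, VECTRON over Fludora.
2. In Data analysis, state the rule in full: take the log of the density ratio in each of the 8 pairs (for the adjusted analysis, the log ratio of observed over expected), form a *t* interval on 7 df, and back-transform. Non-inferiority is declared if the upper limit for the geometric mean ratio is below 1.5.
3. Name the alpha or confidence level and whether it is one-sided.
4. Recalculate and restate the power on the log-ratio scale for 8 pairs, giving the coefficient of variation and the trap-nights used. For orientation, 80% power at k = 0.30 and 49 trap-nights needs 11.24 pairs at one-sided 2.5% (12 after rounding up) or 9.28 at 5% (10).

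Items 1 to 3 are wording changes and cost nothing in the field. Item 4 needs a short recalculation and does not by itself require more clusters, but the expected power should be reported as it is.

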During baseline vector density monitoring, 20 clusters will be included, to improve the pair-matching post-intervention. The four clusters with greatest variance will not be included in the post-intervention monitoring but will still receive the IRS treatment. The 16 selected clusters will be pair-matched based on vector densities and randomly allocated to the two trial arms: one arm (8 clusters) will be sprayed with the novel intervention (VECTRON™ T500) and the other arm (8 clusters), the reference product (Fludora® Fusion). All possible randomisations will be stratified on ITN coverage and wall surface to ensure minimum difference of 15% or less in mean ITN coverage and mean ratio of cement houses to mud houses per arm. From all randomisations that meet these criteria, one will be selected at random.

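### The planned two-stage adjustment, in its usual form, is fitted under a density ratio of 1 although the null is 1.5 or more, so the adjusted ratio leans towards non-inferiority; how far depends on choices the article does not state.

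*Protocol article*

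**What the plan says.** All references are to the protocol article.

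- **Hypothesis** (Power calculation, estimation of effect size and cluster selection): the trial is to show that VECTRON T500 "will not result in higher malaria vector densities, by a prespecified non-inferiority margin of 50" per cent, relative to Fludora Fusion. The null is therefore a density ratio of 1.5 or more.
- **Analysis** (Data analysis): cluster-level summaries, a density ratio for each matched pair, and a paired t-test. The next sentence adds: "Adjustment will be made for time post-spraying, LLIN use and wall type using the two-stage method described by Hayes and Moulton". The stage-1 model, the level of the covariates and the presence of pair terms are not written out.
- **Allocation** (same section as the hypothesis): randomisations are "stratified on ITN coverage and wall surface to ensure minimum difference of 15% or less in mean ITN coverage", with a matching limit on the ratio of cement to mud houses.
- **Data held** (Enumeration of consenting households): nets and wall material are recorded for each house.

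**The concern.** Stage 1 of the two-stage method, as usually applied, regresses the counts on the covariates and leaves the arm out. Stage 2 compares observed/expected ratios between arms. The expected counts are thus built as if the arms did not differ, which is the right null for a superiority test.

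At a true ratio of 1.5 the arms do differ. If LLIN use or wall type also differs between arms by chance, the stage-1 coefficients pick up part of the treatment effect. Stage 2 then sees a log ratio shrunk by roughly the factor 1 - R², where R² is the share of the arm indicator that the covariates explain, but compares it with an unshrunken log 1.5. In a superiority trial this is conservative. Here it raises the chance that a product at the margin is declared non-inferior. Reducing the degrees of freedom does not cure it, because the estimate itself has moved.

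**Working it through.** **Inputs from the article.** Margin ratio 1.5 (log 1.5 = 0.405); "An estimated mean of 3.0 female *Anopheles* per light trap per night will be used"; within-pair CV 0.3, with 0.23 from earlier data ("Previous data suggests a within-pair coefficient of variation of 0.23, but a conservative value of 0.3 will be used in our calculations"); 8 pairs; 180 trap-nights per cluster for the analysis; arm imbalance limited to 15%, read here as percentage points. Time post-spraying is balanced by design, since every cluster is trapped every month.

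**Assumed.** One-sided 2.5%; overdispersed counts; covariate spreads and effects (between-cluster SD of coverage 0.05 to 0.4; effects 0 to -0.7 on the log scale).

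**The plan's own figure first.** The article states "8 clusters per treatment arm (16 in total) will be needed for the 50% margin to have 80% power to demonstrate non-inferiority", and "The calculations were based on 49 trap nights per cluster". The matched-pair formula is

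c = 2 + (z_a + z_b)² × [(l0 + l1)/y + k²(l0² + l1²)] / d²

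With l0 = l1 = 3, y = 49, k = 0.3, d = 1.5 and (1.96 + 0.84)² ≈ 7.85, this gives c = 2 + 7.85 × (0.122 + 1.62)/2.25 = 8.08. The stated 8 is reproduced at one-sided 2.5%. One-sided 5% would give 6.8, so 2.5% is a reasonable working level.

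**Shrinkage by arithmetic.**

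- *Household values.* A binary covariate with prevalence p and arm difference D has R² = D² × 0.25/[p(1 - p)]. At D = 0.15, R² is 0.0225 for p = 0.5 and 0.040 for p = 0.83 (the 2012 ITN ownership figure). A true 1.5 then reads exp(0.405 × 0.9775) = 1.49 or exp(0.405 × 0.96) = 1.48 per covariate, even at the limit of the allowed imbalance.
- *Cluster values with pair terms.* Only 8 within-pair differences carry information, so each covariate absorbs about 1/8 of the log ratio on average. One covariate gives 1.5^(7/8) = 1.43; two give 1.5^(6/8) = 1.36. The allocation limit reduces this somewhat.

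**Error by simulation** (true ratio 1.5, 8 pairs, restricted allocation; stage 1 without an arm term, then a paired t-test against log 1.5):

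| Stage-1 form | Mean adjusted ratio | False non-inferiority |
|---|---|---|
| Unadjusted paired t-test | 1.50 | 2.1-2.8% |
| Both covariates at household level | 1.49-1.50 | 2.1-3.4% |
| Both at cluster level, no pair terms | 1.43-1.46 | 3-5% |
| LLIN at cluster level, pair terms | 1.42-1.43 | 5.4-7.0% (5.0-6.4% with 1 df removed) |
| Both at cluster level, pair terms, CV 0.3 | 1.36-1.41 | 7.3-10.7% (5.9-8.7% with 2 df removed) |
| Stage 1 with log 1.5 offset, 7 df | 1.50 | 2.2-3.1% |

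In the last case before the offset row, some settings (CV 0.23, or other assumed spreads) reached 12-13% before the df correction and up to 11% after it. Regressing the log pair ratios on the within-pair covariate differences gave 2.0-3.0%.

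Forcing the imbalance to 0.10 or 0.15 on both cluster-level covariates gave 12-41% without the offset. Those figures are conditional on a poor draw and are not the error rate of the planned allocation. Under the same forced imbalance, with assumed covariate effects of -0.3, the unadjusted test erred at 4.7-7.5%. It holds its level over the randomisation, not after every draw.

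**The case against.** The strongest case against is that the article names a method in one sentence and leaves the stage-1 model to the full protocol or analysis plan, so no faulty model is on the page. That stands as a limit on size. It does not remove the point: an analysis plan that follows the sentence in the method's usual form inherits the mismatch with the margin.

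Second, nets and wall material are recorded per house, and the Discussion envisages stratifying within clusters by other protective measures. Both support household-level covariates, for which the inflation is negligible. This stands for wall type. It is weaker for LLIN use: the census items are net number and type rather than use, and the Vector density section places traps beside occupied LLINs, so use may vary little between trapped houses. The Discussion also speaks of such tools at community level. Cluster-level LLIN adjustment is plausible but not shown.

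Third, the paired t-test and the adjustment stand in separate sentences, and nothing ties the non-inferiority decision to the adjusted ratio. That also stands.

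A reader might infer that the planned analysis will pass a product at the margin at two to five times the nominal rate. The documents do not support that. Multiples of that order need at least one cluster-level covariate together with pair terms in stage 1, neither of which is stated, and the nominal level is itself an assumption.

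**Conclusion.** The point holds in conditional form. The mismatch between a stage 1 fitted at ratio 1 and a null at 1.5 follows from the usual form of the named method, and its direction is anti-conservative. Its size cannot be fixed from the article. At one-sided 2.5% it is about nominal (2-3.4%) with household values, about 3-5% with cluster values and no pair terms, and about 5-11% with one or both at cluster level and pair terms. These figures rest on assumed covariate spreads and effects, on reading the 15% limit as percentage points, and on the adjusted test being the one that decides. It is worth correcting because it concerns the primary endpoint and the correction is a matter of wording.

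**What to change.** State which paired t-test, adjusted or unadjusted, decides non-inferiority. If it is the unadjusted one, say so, and give the adjusted result a supporting role.

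If the adjusted ratio is to support the claim:

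1. Enter LLIN use and wall type as household (trap-level) covariates where they vary.
2. For the test, fit stage 1 under the margin, with an offset of log 1.5 in the VECTRON arm, and test the residual pair ratios against 1. Reduce the 7 df by one for each cluster-level covariate.
3. Take the adjusted ratio and its confidence limit from a model that includes the arm effect, for example a regression of the eight log pair ratios on the within-pair covariate differences, where the intercept is the adjusted log ratio. The offset version is a test only: by the same mechanism it pulls the estimate towards 1.5. At a true ratio of 1 it would read about 1.5^(1/8) = 1.05 with one cluster-level covariate and 1.5^(1/4) = 1.11 with two.

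**Cost.** A few sentences and no new data. With household-level covariates the loss of power is negligible. With cluster-level covariates it is real and should be stated. At CV 0.3 and a true ratio of 1, the pair-difference regression passes 46% of the time with two such covariates and 55% with LLIN alone, against 65% and 66% for the df-corrected two-stage test. At CV 0.23 the figures are 65% and 74%, against 84% for both. Much of that gap is pass rate that the bias produced.

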**Methods:**

A two-arm non-inferiority cluster randomized controlled trial (Phase III) will be undertaken in Muheza District, Tanga Region, Tanzania. VECTRON™ T500 will be compared to the IRS product Fludora® Fusion (clothianidin 50% WP + deltamethrin 6.25% WP). The predominant malaria vectors in the study area are pyrethroid-resistant *Anopheles gambiae s.s.*, *An. arabiensis* and *An. funestus s.s*. Sixteen village clusters will be pair-matched on baseline vector densities and allocated to reference and intervention arms. Consenting households in the intervention arm will be sprayed with VECTRON™ T500 and those in the reference arm will be sprayed with Fludora® Fusion. Each month, CDC light traps will collect mosquitoes to estimate changes in vector density, indoor biting, sporozoite and entomological inoculation rates (EIR). Susceptibility to IRS active ingredients will be assessed using World Health Organisation (WHO) bottle bioassays. Target site and metabolic resistance mechanisms will be characterised among *Anopheles* field populations from both trial arms. Residual efficacy of both IRS products will be monitored for 12 months post intervention. Questionnaire and focus group discussions will explore factors that influence adherence, adverse effects and benefits of IRS.

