### Study design

A matched cluster randomized controlled non-inferiority study design will be used as IRS in community-level intervention. The study monitoring period will be for 12 months post-intervention or beyond this date if residual efficacy on house walls indicates continuing effectiveness. Baseline data collection on vector densities will commence in the six months preceding the randomisation and pair matching of the clusters. At the onset of the long rainy season, one round of IRS will be done which will be followed by monthly vector density monitoring and *in-situ* cone bioassays. Baseline household enumeration and social-cultural and acceptability measurements will be conducted before IRS.

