## Discussion

Development of new IRS products containing insecticides whose efficacies are not compromised by pre-existing cross-resistance in vector populations is necessary for three reasons: for reinvigorating malaria vector control, for sustaining malaria transmission gains achieved, and for providing opportunity for insecticide resistance management. Establishment of non-inferiority of these new IRS products to WHO PQT/VCP prequalified standards in cluster randomised trials will provide predictive evidence for their community-level performance in the control of malaria vectors against a backdrop of LLIN universal coverage. This protocol describes a non-inferiority two-arm cluster randomised trial of the impact of VECTRON ™ T500 compared to Fludora® Fusion on changes in malaria vector densities and EIR, and evaluates their residual activities.

Since LLINs are the primary means of malaria prevention in Tanzania, it is likely that families within the communities will be using nets or other vector control tools to protect themselves. IRS is a community level intervention; the presence of other vector control tools such as LLINs in families in the two trial arms may affect the ability to measure the relative contribution of the IRS products to reduce vector densities. However, it should be possible to stratify the analysis within each cluster to assess whether there is any additional effect or interaction from secondary vector control or personal protection measures on the effect of IRS [27]. The matched pair allocation of IRS to intervention and reference arms in this trial will take into account such variation of secondary vector control tool usage at community level during random assignment of IRS treatments to clusters.

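### Baseline Anopheles density is measured and used for pairing but is left out of the stage-one adjustment, so residual within-pair baseline differences remain in the primary ratio as avoidable variance

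*Protocol article*

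**What the plan says.** All references are to the protocol article.

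- **Study design.** Baseline density is collected before allocation: "Baseline data collection on vector densities will commence in the six months preceding the randomisation and pair matching of the clusters". The section on power and cluster selection adds that 20 clusters are monitored at baseline, that four are then set aside, and that the remaining 16 are paired on vector density. Allocation is further constrained on ITN coverage and wall surface only.
- **Power calculation.** "Sample size calculations will be based on the study primary endpoint i.e., indoor density of" Anopheles mosquitoes. On variability: "Previous data suggests a within-pair coefficient of variation of 0.23, but a conservative value of 0.3 will be used in our calculations".
- **Vector density (Intervention monitoring).** Non-inferiority is judged on the 180 trap-nights per cluster in the 12 months after spraying.
- **Data analysis.** The density ratio in each pair is tested with a paired t-test on cluster-level summaries. On covariates: "Adjustment will be made for time post-spraying, LLIN use and wall type using the two-stage method described by Hayes and Moulton".
- **Summary text.** The Abstract says "CDC light traps will collect mosquitoes to estimate changes in vector density, indoor biting, sporozoite and entomological inoculation rates (EIR"), and the Discussion describes the trial's impact "on changes in malaria vector densities and EIR, and evaluates their residual activities".

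**The concern.** Baseline density enters the trial only through the pairing. Whatever baseline gap is left within a pair carries into that pair's post-spray ratio to the extent that density persists over time. With 8 pairs the test has 7 degrees of freedom, so leftover gaps widen the confidence interval and can by chance move the estimate towards or away from the margin of 1.5.

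The covariate list is a stated choice, not a silence. It adjusts for LLIN use and wall type even though allocation is already constrained on both in similar form, so the plan accepts adjusting for factors handled in the design. The one omitted is the baseline value of the outcome itself. What is at stake is precision that could be gained from data already collected.

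**Working it through.** **1. The plan's own figure.** Inputs from the power section: mean 3.0 per trap-night, margin 50% (d = 1.5), 49 trap-nights, within-pair CV 0.3, 80% power. Alpha is not stated; one-sided 0.025 is assumed. Matched-pair formula under true equality:

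c = 2 + (1.96 + 0.84)² × [(3 + 3)/49 + 0.3² × (3² + 3²)] / 1.5²
= 2 + 7.85 × (0.122 + 1.620)/2.25
= 2 + 7.85 × 0.774 = 8.08.

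At c = 8 the power is 79.5%. The stated 8 per arm reproduces with no baseline covariate. The CV of 0.3 is the variation left after matching, so it already contains the residual baseline gaps.

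**2. How much variance the gap can carry.** Write the log ratio of pair j as θ + βΔ_j + e_j, where Δ_j is the leftover baseline log difference and β the carry-over. The planned SD of a pair's log ratio is about √(2 × 0.3² + 2/(3 × 49)) = √0.1936 = 0.44. The removable share is β²·SD(Δ)²/0.1936. Simulated pairing of 16 from 20 clusters (between-cluster log SD 0.3 to 1.2) left SD(Δ) of about 0.07 to 0.25. Three examples:

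- SD(Δ) 0.106, β 0.5: 0.0028/0.1936 = 1.5% of variance; SE falls 0.7%.
- SD(Δ) 0.168, β 1: 0.0282/0.1936 = 14.6%; SE falls 7.6%.
- SD(Δ) 0.25, β 1: 0.0625/0.1936 = 32%; SE falls about 18%.

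The result therefore runs from negligible to useful, depending on spread and carry-over, which the documents do not give.

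**3. Simulated power with a pooled slope.** The slope is estimated over all 16 clusters without pair terms, followed by the 7-df paired t-test. Margin 1.5, true ratio 1, one-sided 2.5%. Change in power against no baseline adjustment:

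- Log SD 0.4 to 1.0, carry-over 0.5 or 1, noise 0.2 or 0.3, baseline error 0.15: −0.1 to +2.4 points if the best-matched 16 are kept; +0.2 to +12.4 if the extreme clusters are dropped.
- Noise 0.25, baseline error 0 or 0.2, carry-over 0.5: about 0 to +1 (best-matched) and +1 to +3 (extremes dropped). With carry-over 1, best-matched: about 0 to +5.
- A further run: +0.4 to +3 (best-matched), +1 to +10 (extremes dropped), with type I error 2.1 to 2.9%.

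In the second of these runs, gains near +14 appeared only with full carry-over, log SD 1.0, extremes dropped and no baseline error.

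**4. Two implementations that fail.**

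- *Slope fitted to the 8 pair differences (6 df).* On the log scale with SD 0.44, unadjusted power is 0.61. Adjusted power is 0.51 at a residual correlation of 0, 0.63 at 0.5 and 0.79 at 0.7, with break-even near 0.45. Simulated correlations were about 0.06 to 0.56, and in most settings power fell to between 0.53 and 0.59. It rose (0.62 to 0.69) only with log SD 1.2 and full carry-over. The gap between 0.61 and the planned 80% comes from the scale and the t-test and is a separate matter.
- *Slope fitted with pair indicators, then tested on 7 df.* Type I error rose to about 5.4 to 6.8% against a nominal 2.5%. That slope is estimated from the same 8 within-pair differences that are then tested, and the lost degree of freedom is not charged.

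The pooled slope avoids both problems because it is estimated mainly from variation between pairs, which the paired test does not use.

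**The case against.** The strongest reply is that baseline density is already handled by design. It is the matching factor, extra clusters are monitored to improve the matching, the paired test is valid as planned, and further adjustment is an analyst's choice that could sit in an analysis plan not shown here. Most of this stands. It limits the point to efficiency, and if matching is very good the gain is close to zero. It does not remove the point, because the article itself commits to a covariate list that includes other factors handled in the design and omits this one.

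A reader might also infer stronger claims, which the documents do not support:

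- *The outcome is change from baseline, so the analysis targets the wrong quantity.* The primary objective, the power section, the vector density section and the Data analysis section all define a between-arm comparison of density, with non-inferiority judged on post-spray catches. The references to change in the Abstract and Discussion are loose summary text, not a second endpoint.
- *The trial is underpowered because of the omission.* The CV of 0.3, set above the 0.23 seen in earlier data, already carries this variance.
- *The comparison is biased.* Allocation is random within pairs, so leftover gaps add variance only.
- *The gain could reach 30 points.* That needs the four dropped clusters to be unrelated to matching. This conflicts with the stated purpose of monitoring 20 clusters, and the within-pair CV then reaches up to 0.40, above the plan's 0.3.
- *Baseline density is the strongest predictor available.* This is plausible, but no figure in the documents shows it.

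**Conclusion.** The point holds as a matter of efficiency. The fixed covariate list leaves out a baseline value that is measured in every cluster, so part of the variance in the primary ratio is avoidable. The planned test remains valid and the 8-per-arm figure stands. The expected gain is about 0 to 3 points of power with good matching and up to about 10 with poorer matching, with no material loss. These figures rest on an assumed one-sided alpha of 2.5%, between-cluster log SD of about 0.4 to 1.0, carry-over of 0.5 to 1, and the two readings of which four clusters are set aside. The benefit also depends on the implementation, so that must be specified along with the covariate.

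**What to change.** In Data analysis, extend the adjustment sentence along these lines: *stage one will include log cluster baseline Anopheles density, time post-spraying, LLIN use and wall type; the baseline slope will be estimated over all 16 clusters without pair indicators; stage two will be a paired t-test with 7 degrees of freedom on the adjusted log ratios.* State that the slope will not be fitted to the 8 pair differences, nor with pair terms followed by a 7-df test. Settle this before post-spray data are compared by arm, since adding it after an imbalance is seen would look data-driven. As an editorial matter, align the Abstract and Discussion with the density endpoint.

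The cost is one more prespecified model term, possibly for little gain. No new data, clusters or trap-nights are needed.
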